### Safety assessment

Adverse events of metformin will be closely monitored at each visit during the study (Table 1). The participants will be requested to report any adverse events to the research staff spontaneously. Details of the adverse event and its relationship with the study intervention will be recorded.

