**Fig. 1 Fig1:**
[figure not shown]
Flowchart of the trial. ^#^MRI, questionnaires, and body composition will be acquired. ^☩^262 participants will be enrolled and equally allocated to the two groups (131 per group) in this trial; however, the number of participants actually enrolled may vary slightly. ^*^The follow-up will be carried out at 3, 6, 12, and 24 months, with questionnaires and body composition being acquired at 3, 6, 12, and 24 months, hematological measurements being acquired at 6, 12, and 24 months, and MRI being acquired at 24 months

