### Intervention

Participants in the intervention arm and control arm will take metformin hydrochloride sustained-release tablet (ingredients: microcrystalline cellulose, hydroxypropyl methylcellulose, magnesium stearate, and metformin hydrochloride; Jiangsu Deyuan Pharmaceutical Co., Ltd.) and the identical inert placebo (ingredients: microcrystalline cellulose, hydroxypropyl methylcellulose, magnesium stearate, and lactose; Jiangsu Deyuan Pharmaceutical Co., Ltd.), respectively. The drug and placebo will be administered orally in escalating doses to reduce side-effects and maintain masking: 0.5 g/day for the first 2 weeks, 1 g/day for the next 2 weeks, and then 2 g/day for the remaining period if tolerated. If the subject cannot tolerate the maximum dose (2 g/day), she/he can take their maximum tolerable dose. In case of adverse reaction or deteriorated hepatic and renal function, the researchers can determine whether the subject needs to reduce or stop the drug based on their discretion.

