Hematological measurements: Fasting morning blood samples will be collected at the screening and 6, 12, 24-month follow-up. Serum levels of alanine aminotransferase and aspartate aminotransferase and estimated glomerular filtration rate will be tested at the above time points to reflect the hepatic and renal function. Besides, at the screening and 24-month follow-up, blood lipid profile and C-reactive protein will be tested and serum will be isolated and stored at − 80 °C for further measurement of inflammatory cytokines (e.g., tumor necrosis factor**-**α, interleukin-1, interleukin-6) and adipokines (e.g., leptin, resistin, visfatin).

Concomitant medication: Concomitant medication usage will be not restricted in this study, but will be documented at the baseline and each follow-up.

Pill counts: The pill counts will be recorded to infer the medication compliance of the participants.

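### Adverse events are said to be closely monitored at visits, but the only collection method named is spontaneous participant report, and both dose steps precede the first follow-up visit

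*Protocol article*

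**What the plan says.** The Safety assessment section of the protocol article has three operative sentences. The first sets the occasions: "Adverse events of metformin will be closely monitored at each visit during the study (Table 1". The second gives the method: "The participants will be requested to report any adverse events to the research staff spontaneously". The third says what is kept: "Details of the adverse event and its relationship with the study intervention will be recorded".

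The Fig. 1 legend gives the schedule: "The follow-up will be carried out at 3, 6, 12, and 24 months". Table 1 ticks adverse events at months 0, 3, 6, 12 and 24.

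The Intervention section says that drug and placebo are "administered orally in escalating doses to reduce side-effects and maintain masking", in these steps: "0.5 g/day for the first 2 weeks, 1 g/day for the next 2 weeks, and then 2 g/day for the remaining period if tolerated". A participant who cannot tolerate the top dose may stay on a lower one. After an adverse reaction, "the researchers can determine whether the subject needs to reduce or stop the drug based on their discretion".

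The Data integrity and management section plans safety analyses by masked group.

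**The concern.** The first two sentences of the section do not fit well together. Close monitoring at a visit suggests that staff ask. Spontaneous report means that the participant volunteers. No standard question, checklist or recall period accompanies either sentence. This is a stated choice of method, not only a detail left to another document.

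The choice matters because tolerability governs exposure in this trial. The escalation is there to limit side-effects, and its last step depends on tolerance. Yet no follow-up visit falls inside the four weeks of escalation. A mild complaint that leads someone to settle at a lower dose may never be volunteered, or may be volunteered at some of the seven sites and not at others.

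At stake are the absolute event rates and the precision of the comparison between arms. The Discussion looks ahead to metformin as a disease-modifying drug for knee osteoarthritis, and the trial excludes people with diabetes. How often such participants have symptoms on the drug is part of what a reader will want from it.

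**Working it through.** **1. Timing, from the documents.** Visits are at months 0, 3, 6, 12 and 24, so the gaps are 3, 3, 6 and 12 months. The dose rises after week 2 and after week 4. Taking 3 months as about 13 weeks, the first follow-up visit comes about 13 − 4 = 9 weeks, or two months, after the last step. The window that matters for escalation events is therefore months 0 to 3. The 12-month gap applies only to months 12 to 24.

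**2. Method, from the documents.** Spontaneous report is the only route named for symptomatic events. Two other sources exist but do not fill the gap. Liver and renal tests do not rely on the participant ("Fasting morning blood samples will be collected at the screening and 6, 12, 24-month follow-up"), but they do not detect symptoms. Pill counts show that intake fell, not why.

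**3. Effect of incomplete capture (illustration).** The plan gives no adverse-event rate, capture fraction or safety power, so there is no figure of its own to reproduce. The only input from the documents is n = 131 per arm (Sample size), used here without loss to follow-up. The true risks p₁ and p₀ and the captured share s, equal in both arms, are assumptions.

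The observed risks are s·p₁ and s·p₀. The risk ratio is s·p₁ / s·p₀ = p₁/p₀, so s cancels. The risk difference is s·(p₁ − p₀), so it shrinks in proportion to s.

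Power, two-sided 0.05, normal approximation: Φ[(d − 1.96·SE₀)/SE₁], where d is the observed difference, SE₀ = √(2·p̄(1 − p̄)/n) with p̄ the mean of the two observed risks, and SE₁ = √([a(1 − a) + b(1 − b)]/n) with a and b the observed risks.

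- s = 1.0, 30% v 15%: (0.150 − 1.96 × 0.0516)/0.0508 ≈ 0.96, power 83%
- s = 0.8, 24% v 12%: (0.120 − 1.96 × 0.0475)/0.0469 ≈ 0.57, power 72%
- s = 0.5, 15% v 7.5%: (0.075 − 1.96 × 0.0390)/0.0388 ≈ −0.04, power 48%

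The risk ratio is 2.0 in all three rows.

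**4. Range over other assumed risks.**

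| True risks | s = 1.0 | s = 0.8 | s = 0.6 | s = 0.4 |
|---|---|---|---|---|
| 30% v 10% | 98% | 95% | 85% | 67% |
| 20% v 10% | 62% | 51% | 40% | 28% |
| 15% v 5% | 77% | 67% | 53% | 38% |

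The direction is the same throughout. The size depends on the assumed risks: a large excess survives moderate under-capture, and a smaller one does not.

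**The case against.** The section can be read as two complementary routes: monitoring at visits, and reporting by participants whenever something happens. On that reading spontaneous report need not wait for a visit, and the gaps between visits are not recall periods. The text also asks for any adverse event and records its relationship to treatment, which implies recording first and judging cause second. Researchers decide on dose changes after an adverse reaction, and reasons for withdrawal are recorded, so some tolerability problems do reach staff. The Quality assurance section mentions a standard protocol, a manual of operating procedures and a case report form, none of them shown; a standard question may be there. All event rates and capture fractions above are assumed, and the trial is sized on efficacy alone.

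Much of this stands. It rules out three stronger conclusions that a reader might draw:

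- That the safety comparison is unreliable. Participants and investigators are blinded and the method is the same in both arms, so equal under-capture leaves the risk ratio intact. Bias would need differential reporting, for instance if side-effects reveal the allocation, and nothing in the document shows that.
- That escalation events are exposed to a 12-month recall window. They fall in the first three months.
- That reasons for dose reduction are lost. They may be under-documented for a participant who settles at a lower dose, but loss is not shown.

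What does not fall is the sentence itself. An unseen manual can excuse silence, but here the article states a method and it is the passive one. If the manual does require a standard question, this section still misdescribes the collection and needs aligning. Reporting between visits still depends on each participant's initiative.

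**Conclusion.** The point holds in a limited form. The article names spontaneous report as its only way of obtaining symptomatic adverse events, this sits badly with its promise of close monitoring at visits, and both dose steps come before the first follow-up visit. Under-counting of mild symptoms is likely, but its extent cannot be derived from the document.

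If it is equal between arms, the consequence is understated absolute rates, a smaller risk difference and lower power: in the main illustration 83% falls to 72% or 48%, with the risk ratio unchanged. Those figures rest wholly on assumed risks, assumed capture and no loss to follow-up. That the missed events would be mainly gastrointestinal is also an assumption, since the document does not say which side-effects it expects. No efficacy analysis or sample size is touched. This is a worthwhile and cheap improvement, not a flaw that invalidates the trial.

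**What to change.** Reconcile the first two sentences of the Safety assessment section. State that at every visit ticked for adverse events in Table 1:

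- blinded staff ask each participant the same open question about health since the last contact, followed by a short fixed gastrointestinal checklist;
- every event is recorded regardless of suspected cause, with its onset date and any dose change that went with it, and relatedness is judged afterwards;
- spontaneous reporting between visits continues as an addition.

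Onset dates let the month-3 visit place events within the escalation period, although about two months of recall remain. If the manual or case report form already contains such a prompt, only the wording here needs to change.

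The cost is a few minutes at visits already scheduled and a page of the case report form. The downside is that more minor events will be recorded in both arms. No dose or clinical rule changes.

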### Sample size

The sample size calculations were performed using the formula: n_1_ = n_2_ = 2 × [(Z_α_ + Z_β_) × σ/δ]^2^ and assumed α = 0.025 (one-sided) and β = 0.20 (Z_α_ = 1.96; Z_β_ = 0.842).

According to a previous study, the standard deviation of annual tibiofemoral cartilage volume loss in obese knee OA patients was 1.92% (σ), and taking metformin could decrease the average annual tibiofemoral cartilage volume loss by 1.07% (δ) [22]. Considering that it may take a long time for metformin to exert the protective effect on articular cartilage, we assumed that the volume of articular cartilage begins to differ after 1 year of metformin use, that is, the second year of follow-up can be used to observe the effect of metformin on the articular cartilage volume. Based on the assumption and the data from the previous study, we calculated that 51 participants per group (n_1_, n_2_) are needed.

Sample size calculation was also performed based on another primary outcome, namely, WOMAC score. Up to now, no study has reported the effect of metformin on WOMAC score. We hypothesized that metformin treatment for 2 years will have more decrease in WOMAC score compared with placebo. The minimum clinically important difference (MCID) of WOMAC score in patients with knee OA was reported being 12, 14, 16, 18, and 20% of the baseline score [29–33]. Combined, we took the 16% for sample size calculation. In our previously established Chinese symptomatic knee OA cohort, the mean baseline WOMAC score was 99.95 (a total score of 240) [28]. Based on these data, it is estimated that the difference in the changes in WOMAC score (a total score of 2400) between metformin and placebo groups needs to be greater than 159.92 (δ) to achieve MCID. In our previous clinical trials for patients with knee OA, the standard deviation of change from baseline to two-years follow-up of WOMAC score was 413.74 (σ). Therefore, the sample size was calculated as 105 for each group (n_1_, n_2_).

Take into consideration of these two calculations and a 20% dropout over the trial, 131 participants in each arm will be sufficient to detect the differences of primary outcomes between the two groups.

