### Outcome measures

Primary outcomes will be changes in tibiofemoral cartilage volume and WOMAC score over 24 months. Secondary outcomes will be changes in VAS knee pain, tibiofemoral cartilage defects, effusion-synovitis volume, and tibiofemoral bone marrow lesions maximum size over 24 months.

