#### Assessment of knee structures

Knee structural changes will be assessed using MRI at baseline and 24-month follow-up (Table 1). MRI sequences sensitive for cartilage [e.g., 3D dual-echo in steady state (DESS) or 3D Water Selected fluid (WATSf) sequences] will be used to assess tibiofemoral cartilage volume. MRI sequences sensitive for detailed anatomy [e.g., 2D intermediate-weighted fat suppression or 2D proton density-weighted fat suppression sequences] will be used to assess tibiofemoral cartilage defects, effusion-synovitis volume, and tibiofemoral bone marrow lesions maximum size. All these knee structures will be assessed on the sagittal images. Besides, coronal sequences sensitive for detailed anatomy will be also acquired to assist sagittal images positioning. Details of MRI sequences and parameters will be determined according to the magnetic resonance (MR) scanner available at each site. Before the enrollment, the specific MRI sequences and parameters will be tested in corresponding MR scanners to ensure the MR image meets the study requirement.

**Table 1 Tab1:** Schedule of data collection

	Screening	months				
		0	3	6	12	24

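### The cartilage sample size uses a one-year SD for an endpoint measured over 24 months, so neither the 51 per group nor the sufficiency of 131 per arm for cartilage follows from the stated inputs.

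*Protocol article*

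**What the plan says.** The Sample size section of the protocol article gives a standard two-means formula with one-sided alpha 0.025 and 80% power. For cartilage, the variability input is annual: "the standard deviation of annual tibiofemoral cartilage volume loss in obese knee OA patients was 1.92% (σ". So is the effect: "taking metformin could decrease the average annual tibiofemoral cartilage volume loss by 1.07% (δ". The authors then assume that volumes start to diverge only after a year of treatment, so that "the second year of follow-up can be used to observe the effect of metformin on the articular cartilage volume". From this, "we calculated that 51 participants per group" are needed.

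The WOMAC calculation in the same section uses the SD of the two-year change (413.74) and arrives at 105 per group. Allowing for 20% dropout, the section concludes that 131 per arm is enough for the primary outcomes.

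The endpoint is defined under Outcome measures: "Primary outcomes will be changes in tibiofemoral cartilage volume and WOMAC score over 24 months". The scan schedule is under Assessment of knee structures: "Knee structural changes will be assessed using MRI at baseline and 24-month follow-up". Table 1 and the legend to Fig. 1 agree that there is no 12-month MRI. The Statistical analysis plan section compares the groups on change from baseline to follow-up.

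**The concern.** The calculation is set up as if second-year loss were the outcome. Without a 12-month scan, that quantity cannot be separated from first-year loss. What will be analysed is the full 24-month change. Under the stated lag, the expected difference in that change is 0 + 1.07 = 1.07 points. Its SD is that of two years of loss, and the protocol does not give that figure. Using the one-year SD in its place makes the cartilage outcome look comfortably powered unless two-year loss varies no more than one-year loss.

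Cartilage volume is co-primary and is the structural half of the trial's question. If its power is well below what the section implies, a non-significant cartilage result would be less informative than a reader of the protocol would expect.

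**Working it through.** **Inputs.** All are from the Sample size section unless noted.
- Formula: n per group = 2 × [(Zα + Zβ) × σ/δ]², with Zα = 1.96 and Zβ = 0.842.
- σ = 1.92 (annual) and δ = 1.07 (annual).
- Lag: no difference in year 1.
- Evaluable per arm: 131 × 0.8 = 104.8, about 105.
- Endpoint and scans: 24-month change, MRI at months 0 and 24 (Outcome measures; Assessment of knee structures).

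**Step 1: reproduce the stated figure.** 2 × [(1.96 + 0.842) × 1.92/1.07]² = 50.56, rounded up to 51. The arithmetic is right, and so is the step to 131 (105/0.8 = 131.25). The fault is in the time scale of σ. With these inputs, power at 105 per group would be 98%.

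**Step 2: put δ on the endpoint's scale.** Over 24 months with a one-year lag, δ = 0 + 1.07 = 1.07 points.

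**Step 3: put σ on the endpoint's scale.** Assume that 1.92% is the SD of loss over a one-year interval and is the same in both years. Let ρ be the correlation between a patient's year-1 and year-2 loss. Then:

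SD of 24-month change = 1.92 × √(2(1 + ρ))

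The protocol does not give ρ, so a range is shown.

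**Step 4: recompute.** Power at 105 per group = Φ(1.07/(SD × √(2/105)) − 1.96). Detectable difference at 80% power = 2.802 × SD × √(2/105).

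| ρ (assumed) | 24-month SD | n per group | Enrolled per arm (n/0.8) | Power at 105 | Detectable difference (points) |
|---|---|---|---|---|---|
| −0.5 | 1.92% | 51 | 64 | 98% | 0.74 |
| −0.25 | 2.35% | 76 | 95 | 91% | 0.91 |
| 0 | 2.72% | 102 | 128 | 81% | 1.05 |
| 0.5 | 3.33% | 152 | 190 | 65% | 1.29 |
| 1 | 3.84% | 203 | 254 | 52% | 1.48 |

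Example for ρ = 0: 1.92 × √2 = 2.715, and 2 × [2.802 × 2.715/1.07]² = 101.1, rounded up to 102.

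**Step 5: read the rows.**
- ρ = −0.5 is the case where all the variation is scan error. The month-12 error enters the two yearly losses with opposite signs and cancels over 24 months. Only here does 51 stand.
- ρ = 0 means independent yearly losses.
- ρ = 1 means each patient loses cartilage at a constant personal rate.

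**Step 6: find the break-even.** With 105 per arm, 80% power needs SD ≤ (1.07/2.802) × √(105/2) = 2.77%. That corresponds to ρ ≤ 2.77²/(2 × 1.92²) − 1, about 0.04.

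**The case against.** **Recruitment rests on WOMAC, not on the 51.** True: 105 evaluable is already about twice 51. If yearly losses are independent, 128 enrolled per arm are needed and 131 covers it. This stands as a limit on the point. It does not rescue the derivation, because the section relies on both calculations when it calls 131 sufficient.

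**Part of the annual SD may be measurement error.** This also stands. It pulls ρ below 0 and the 24-month SD below 2.72%, as the −0.25 row shows. The protocol does not argue it and gives no error share.

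**Covariate adjustment and return visits may help.** The model adjusts for baseline value, age, sex and BMI, and participants who withdraw after 6 months are asked back at month 24. Both could raise power, but no gain is stated. Bringing the residual SD back to 1.92% would require explaining 1 − (1.92/2.715)² = 50% of the variance at ρ = 0, or 1 − (1.92/3.84)² = 75% at ρ = 1. With all 131 per arm evaluable, power would be 89% at ρ = 0 and 62% at ρ = 1.

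**The effect may run through both years.** With δ = 2.14 and σ = 3.84 the formula again gives 51. The protocol's lag assumption rules this out.

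**Readings that go too far.** A reader might annualise the contrast and set 0.535% per year against 1.92% per year. That describes only ρ = 1; with independent years the annualised SD is 2.72/2 = 1.36%. A reader might also treat 52% to 81% as the trial's power. Nothing in the document confines ρ to between 0 and 1, so those figures are not bounds.

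**Conclusion.** The point holds as a mismatch of inputs, not as an arithmetic error. One year's SD is applied to a two-year change that, by the protocol's own assumption, carries one year of effect. The 51 per group does not follow for the stated endpoint. Nor does the claim that 131 per arm is sufficient for cartilage.

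A reader might infer that 131 per arm is too few. The document does not support that. Sufficiency turns on whether the 24-month SD is above or below about 2.77%, and the protocol does not say. Under the one-year-interval assumption, the illustrations run from 76 per group and 91% power (ρ = −0.25) to 203 per group and 52% power (ρ = 1).

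The interval over which the source cohort measured its annual SD is not stated either. If the figure was annualised from scans further apart, the conversion changes; for scans two years apart the 24-month SD would be 2 × 1.92 = 3.84%.

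**What to change.** In the Sample size section:
- Replace the annual SD with the SD of 24-month tibiofemoral cartilage change from the source cohort. If that is unavailable, state the assumed between-year correlation and the interval behind the 1.92%.
- Recompute the cartilage number with δ = 1.07 points over 24 months, and remove the 51.
- State the cartilage power, or the difference detectable with 80% power, at about 105 evaluable per arm. Label any range as resting on an assumed correlation.
- If the 24-month SD exceeds about 2.77%, qualify the sentence that 131 per arm is sufficient so that it no longer covers cartilage at 80% power.

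The cost is rewording and possibly a less favourable stated power. No extra patients or scans are needed.

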### Statistical analysis plan

Baseline characteristics will be reported per group using descriptive statistics (means, proportions, and medians as appropriate) without statistical tests.

The primary analyses will be intention-to-treat analyses of primary and secondary outcomes. Per-protocol analyses will be performed as the secondary analyses, and participants with an average daily dose of 0.5-2 g of the investigational drug will be included in the per-protocol analyses. Missing data caused by loss to follow-up and nonresponses will be addressed by multiple imputations with chained equations. Imputations will be performed separately for each treatment group and each outcome using baseline variables of age, sex, BMI, and study site and non-missing values of the outcomes at baseline and each follow-up with the assumption of data missing at random. The treatment effect will be analyzed using linear mixed effect models. In the models, baseline covariates (age, sex, BMI, baseline value of the corresponding outcome), treatment, month, and the interactions of covariates and treatment with month will be entered as fixed effects. The correlation within the study sites and the repeated measures will be addressed using trial site and participant identification as random intercepts. Month will be treated as random slope to allow different treatment effects among knee OA patients over time. Changes in outcome measures within each group and difference of the changes between groups from baseline to follow-up will be calculated using linear combinations of the estimated coefficients.

Pre-specified stratified analyses will be performed to explore whether BMI could affect the treatment effect of metformin on knee OA. This will be conducted by introducing a 3-way interaction between treatment, month, and BMI in the linear mixed-effects models.

Because of the potential for type I error due to multiple comparisons, the findings for the analyses of the secondary outcomes and the stratified analyses will be interpreted as exploratory. A 2-sided *P* value of 0.05 or less will be considered as statistically significant.

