#### Assessment of knee symptoms

Knee symptoms will be assessed by WOMAC score and VAS knee pain at baseline and 3-month, 6-month, 12-month, and 24-month follow-up (Table 1).

The WOMAC system in a 100-mm visual analog format will be used to quantify the degree of knee pain (5 questions), joint stiffness (2 questions), and physical dysfunction (17 questions) during the last 7 days [26]. The WOMAC score will be calculated by summing the score of each question (1 point for every 1 mm), and a higher score of WOMAC represents a more severe OA symptom. The WOMAC score will be considered invalid and treated as missing data if more than 5 of the questions are not answered. In case no more than 5 items are missed, the remaining items will be averaged and then multiplied by 24 to create the WOMAC score.

The 100 mm VAS will be used to assess the knee pain during the last 7 days, and a higher VAS indicates a more severe knee pain.

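### Imputed outcome by outcome, a missing 24-month cartilage volume has no post-baseline predictor, so for the MRI outcomes multiple imputation adds essentially nothing to the mixed model

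*Protocol article*

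**What the plan says.** The Statistical analysis plan section of the protocol article handles missing data by chained-equations multiple imputation: "Imputations will be performed separately for each treatment group and each outcome using baseline variables of age, sex, BMI, and study site". The sentence goes on to add "non-missing values of the outcomes at baseline and each follow-up with the assumption of data missing at random".

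The measurement schedules differ by type of outcome:

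- MRI outcomes (cartilage volume, cartilage defects, effusion-synovitis volume, bone marrow lesion size): "Knee structural changes will be assessed using MRI at baseline and 24-month follow-up".
- Symptom outcomes: "Knee symptoms will be assessed by WOMAC score and VAS knee pain at baseline and 3-month, 6-month, 12-month, and 24-month follow-up".
- Adherence, under Other measurements: "The pill counts will be recorded to infer the medication compliance of the participants". Table 1 schedules this at every visit from baseline.

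The analysis model is described so: "In the models, baseline covariates (age, sex, BMI, baseline value of the corresponding outcome), treatment, month", with interactions with month, and with site handled by "using trial site and participant identification as random intercepts". The Sample size section allows for "a 20% dropout over the trial". The Withdrawal section asks participants who leave after month 6 to return for the 24-month assessment, and uses those data.

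**The concern.** Multiple imputation improves on a mixed model fitted to the observed data only if the imputation model contains something that the analysis model lacks. WOMAC and knee VAS have their own values at 3, 6 and 12 months to draw on. Cartilage volume has one value before month 24, the baseline, and that is already a covariate. If each outcome is imputed only from its own series, imputation for a co-primary outcome is redundant, and missing at random must hold given age, sex, BMI, site and baseline volume alone.

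At stake is the between-arm cartilage comparison. If interim symptoms were related both to who misses the final scan and to cartilage loss, and if the first relation differed by arm, the comparison would be biased. The planned imputation would not reduce that bias, although the trial collects data that could.

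**Working it through.** **1. The plan's own figures.** These confirm the inputs but do not bear on the imputation.

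- Cartilage: n = 2 × [(1.96 + 0.842) × 1.92 / 1.07]² = 50.56, so 51 per arm, as stated.
- WOMAC: n = 2 × [(1.96 + 0.842) × 413.74 / 159.92]² = 105.10, stated as 105.
- Dropout: 105 / 0.8 = 131.25, stated as 131. Conversely, 131 × 0.8 = 104.8 observed per arm.

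**2. The two models side by side, for a missing 24-month cartilage volume.**

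| Information | Imputation (own series only) | Analysis model |
|---|---|---|
| Age, sex, BMI | yes | yes |
| Site | yes | yes (random intercept) |
| Baseline cartilage volume | yes | yes |
| Treatment | yes (imputed by arm) | yes |
| Any value from 3, 6 or 12 months | no | no |

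The imputation model holds nothing that the analysis model lacks.

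**3. Simulation.**

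- From the document: 131 per arm, effect 1.07, SD 1.92, 20% missing at 24 months, imputation by arm.
- Assumed, not in the document: metformin dropout is random; placebo dropout depends on symptom worsening (log-odds 1.0 per SD); symptom worsening correlates r with cartilage loss, r from 0 to 0.5.
- Simplifications: a 24-month analysis of covariance stands in for the mixed model, site is left out, baseline covariates are unrelated to the outcome, and the symptom value is known for everyone. The last point makes the gain shown a ceiling.
- There were 1,000 runs with 20 imputations each. Monte Carlo error of each mean is about 0.27 / √1000 = 0.009.

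| r | No missing data | Observed data only | Imputation, baseline only | Imputation plus symptom value |
|---|---|---|---|---|
| 0 | 1.059 | 1.061 | 1.060 | 1.061 |
| 0.1 | 1.080 | 1.050 | 1.051 | 1.084 |
| 0.3 | 1.079 | 0.979 | 0.980 | 1.080 |
| 0.5 | 1.062 | 0.893 | 0.895 | 1.063 |

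**4. Reading the table.**

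- Baseline-only imputation against observed data: equal means, estimates correlated 0.99, mean SE larger by 0.003 to 0.004. No bias is removed and no precision gained.
- Bias of baseline-only imputation against the no-missing-data result, as a share of 1.07: r = 0, none; r = 0.1, 0.029 / 1.07 = 3%; r = 0.3, 0.099 / 1.07 = 9%; r = 0.5, 0.167 / 1.07 = 16%. The direction is toward the null, because placebo loses participants with more cartilage loss.
- Against an SE of about 0.27, the largest bias is 0.167 / 0.27 = 0.6 of a standard error.
- The symptom auxiliary removes the bias where there is one. Where r = 0 it changes the mean SE only from 0.272 to 0.275.

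**The case against.** **The wording is not closed.** The predictor clause speaks of outcomes in the plural, whereas the analysis-model sentence refers to the one corresponding outcome. The plural could admit interim WOMAC and VAS when cartilage volume is imputed. This stands as an ambiguity. Imputing separately for each outcome points more naturally to each outcome's own series. Pill counts are not outcomes, so they stay out on either reading.

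**The Withdrawal section limits the problem.** Recalling those who leave after month 6 reduces missing scans. To the extent that it works, the remaining gaps come mainly from early withdrawals, who have a month-3 value at best or little more, so the auxiliaries carry least information where they are most needed. This stands, and it makes the benefit modest. Those who leave by month 6 are not recalled, and later ones may decline.

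**Nothing shows that symptoms or adherence drive dropout.** A reader might infer that they do. No section says what drives dropout or that it differs by arm, so this is an assumption here.

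**The bias can be made to look larger.** A reader might suppose that one arm loses exactly its worst fifth on symptoms while the other loses a fifth at random. The completer mean then shifts by r × SD × 0.350. With r of 0.1 to 0.3 and SDs of 2.72 to 3.84 (1.92 × √2 and 1.92 × 2), that is 0.10 to 0.40 points, or 9% to 38% of 1.07. The document gives neither the hard truncation nor those SDs. With its own 1.92 the same formula gives 0.07 to 0.20 points, or 6% to 19%.

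**This could be detail left to a fuller plan.** In part, yes. But the article does more than stay silent: it names the predictors and the outcome-by-outcome rule.

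**Conclusion.** The point holds in a limited form. On the natural reading, imputation for cartilage volume and the other MRI outcomes essentially reproduces the result from observed data, and missing at random rests on baseline variables alone. That part follows from the stated models and schedule. It does not extend to WOMAC or knee VAS, so it would be wrong to conclude that multiple imputation is useless in this trial. Nor does redundant imputation itself create bias.

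The size is conditional. Bias of about 0% to 16% of the 1.07-point effect, toward the null, requires symptom-dependent dropout in the placebo arm only and a correlation of 0 to 0.5 between symptom worsening and cartilage loss. With other patterns of dropout the size and direction could differ. The figure also uses the plan's SD of 1.92, which is an annual value; bias in points scales with the SD. The recall after month 6 and the sparse interim data of early withdrawals reduce what a better imputation model can recover.

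**What to change.** State whether interim symptom values enter the imputation of the MRI outcomes, and make the answer yes. Keep imputation within arm. When imputing 24-month cartilage volume and the other MRI outcomes, add WOMAC and knee VAS at 3, 6 and 12 months as auxiliary variables and, if feasible, one summary of pill-count adherence. Fix this in writing before the first step of unblinding.

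Keep the auxiliary set small. Age, sex, BMI and baseline volume take 4 coefficients, and the seven listed sites take 6. Six interim symptom values and one adherence summary bring the total to 4 + 6 + 6 + 1 = 17, against about 105 observed scans per arm. A single system holding every outcome, weight at each visit and more would be large for 131 per arm and is not needed.

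The cost is somewhat more programming and a slightly larger imputation model. No new data, visits or participants are required.
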